### Randomization and blinding

Participants will be randomly assigned to either one of the two stimulations or the control group with a 1:1: sqrt(2) allocation, as per a computer generated randomization schedule stratified by the study center using permuted blocks of random sizes. The block sizes will not be disclosed, to ensure concealment. We will use Zelen’s design, in which randomization occurs before informed consent. Those patients in the control group (n = 42) receiving standard care will not be consented for participation in this study. They will be informed in an observational study with questionnaires to provide the same measurements, except for treatment, as that in the treatment groups for free, and thus blinded. Other participants who accept the intervention will provide further informed consents, in which they will be informed to have the possibility of receiving either one of the two stimulations according to computerized randomization schedule. The two stimulation groups will include the tan-VNS group (n = 30) and the ta-VNS group (n = 30). Participants in the control group and stimulation groups are thus blinded.

The randomization sequence will be generated using SPSS v.17.0 software (IBM, Armonk, NY, USA) and distributed in a sealed envelope to the doctor. The researchers will not be permitted to change it after the patients are randomized. Employees outside the research team will feed original data into the computer in separate datasheets so that the researchers can analyze data without having access to information about the allocation. The evaluation of the curative effect and the statistical analysis will be evaluated by a third party in the clinical evaluation center of the China Academy of Chinese Medical Sciences who will not know the grouping and patients. In this clinical trial process, the patients, statisticians and the assessor for statistical data and outcomes will be blind to treatment allocation. Allocation concealment will not be exposed until the final data analysis report is completed.

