### Outcome measures

#### Primary outcomes

Seizure frequency: the baseline seizure frequency and the seizure frequency after 2 months, 4 months and 6 months of enrollment will be counted according to the patient’s seizure diary. Seizure outcomes will be expressed with a modified Engel scale [12].

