### Statistical analysis

The intention-to-treat population will be defined as the participants who are randomized and received at least one treatment session. An interim analysis will be performed on the primary endpoint when 50 % of patients have been randomized and have completed the 1.5 years’ follow-up. The interim analysis will be performed by an independent statistician, blinded for the treatment allocation. All statistical calculations will be performed using SPSS v.17.0. Comparison of seizure frequency, HRV and QOL between baseline and after treatment will be analyzed by paired-samples t-test. The Kolmogorov-Smirnov test will be used to evaluate if groups fit normal distributions. Normally distributed groups will be analyzed by parametric tests. Comparisons between the three groups will be analyzed by one-way ANOVA followed by Student–Newman–Keuls or Dunnett’s T3 post-hoc tests. Non-normally distributed groups will be analyzed by Mann–Whitney’s test. The factors that affect curative effect will be analyzed with the multinomial logistic regression method. A *P* value <0.05 will be considered of statistical significance.

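### Non-normal outcomes in this three-arm trial go to a two-sample test with no overall test or adjustment: about 12% false positives at one visit if any significant pair counts

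*Protocol article*

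**What the plan says.** The Statistical analysis section of the protocol article sets up two routes. The route depends on a normality check: "The Kolmogorov-Smirnov test will be used to evaluate if groups fit normal distributions". On the normal route, "Comparisons between the three groups will be analyzed by one-way ANOVA followed by Student–Newman–Keuls or Dunnett’s T3 post-hoc tests". On the other route, "Non-normally distributed groups will be analyzed by Mann–Whitney’s test". No three-group rank test is named. The only criterion is that a P "value <0.05 will be considered of statistical significance".

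The Randomization and blinding section defines three arms "with a 1:1: sqrt(2) allocation": 30 on ta-VNS, 30 on tan-VNS and 42 controls. The Primary outcomes section says that "the baseline seizure frequency and the seizure frequency after 2 months, 4 months and 6 months of enrollment will be counted", without ranking the three post-baseline visits, and adds: "Seizure outcomes will be expressed with a modified Engel scale".

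**The concern.** Mann-Whitney cannot answer a three-group question. In practice it becomes three pairwise tests (ta-VNS against tan-VNS, ta-VNS against control, tan-VNS against control), each at 0.05. The parametric route asks first whether the three arms differ at all and only then looks at pairs. The two routes therefore carry different error rates, and the data decide which one applies.

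The weaker route is the likelier one on the article's own facts. Entry requires at least eight seizures in 2 months and sets no upper limit, which favours a long right tail. In the adult pilot cited in the Background, 8 of 47 patients (17%) became seizure-free, so a cluster at zero during follow-up is plausible.

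At stake is whether a significant result for seizure frequency carries the 5% error rate that readers will assume.

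**Working it through.** **Inputs from the article.** Arms of 30, 30 and 42 (check: 30 × √2 = 42.4, which agrees with 42; total 102). Threshold 0.05 per test. Primary visits at 2, 4 and 6 months.

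**Assumptions.** Two-sided tests, no true difference between arms, log-normal data, equal correlation ρ between every pair of visits. The article gives no ρ, so the whole range is shown.

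**Step 1: simple bound.** If tests were independent, the chance of at least one false positive is 1 − 0.95^k. For k = 3 this is 14.3%; for k = 9 (three pairs × three visits) it is 37.0%. Both overstate the rate, because pairs share arms and visits share patients.

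**Step 2: simulation, 20,000 trials for each ρ.** One pair at one visit gives 4.7% to 5.1%. This reproduces the nominal 5%, so the test itself is sound and any excess comes from repetition.

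| ρ | 3 pairs, 1 visit | 3 pairs, any of 3 visits | ta-VNS vs tan-VNS only, any of 3 visits | Kruskal-Wallis first, 1 visit | Kruskal-Wallis first, any of 3 visits |
|---|---|---|---|---|---|
| 0 | 12.3% | 32.0% | 13.7% | 5.0% | 13.8% |
| 0.5 | 12.1% | 29.0% | 12.9% | 5.0% | 12.7% |
| 0.7 | 11.9% | 25.4% | 11.0% | 4.9% | 11.0% |
| 0.9 | 11.9% | 20.1% | 8.4% | 4.6% | 8.4% |
| 1 | 12.2% | 12.2% | 4.8% | 4.9% | 4.9% |

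The one-visit figure does not depend on ρ; differences down that column are simulation error. If only the two contrasts involving ta-VNS count, the rate is about 9% at one visit and 22% over three visits at ρ = 0.5.

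**Step 3: does the normality check cause the excess?** In 1,500 simulated trials per distribution at one visit, each arm was tested with the Lilliefors form of Kolmogorov-Smirnov. Any failure sent all three pairs to Mann-Whitney; otherwise ANOVA was used.

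| Data | Trials sent to Mann-Whitney | False positives, any pair |
|---|---|---|
| Normal | 13.1% | 7.8% |
| Log-normal, log-SD 0.3 | 56.7% | 10.2% |
| Log-normal, log-SD 0.5 | 90.7% | 10.8% |
| Log-normal, log-SD 1 | 100% | 12.7% |

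The check holds the rate below 12% when data are near normal and lets it reach about 12% when they are skewed. It does not add to it.

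**Step 4: how often would arms split?** For log-normal data with log-SD 1, the probability that an arm of 30 or 42 fails is 0.93 or 0.985 (Lilliefors) and 0.42 or 0.68 (uncorrected Kolmogorov-Smirnov). P(split) = 1 − P(all fail) − P(none fail).

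- Lilliefors: 1 − 0.93² × 0.985 − 0.07² × 0.015 = 1 − 0.852 − 0.000 = 15%.
- Uncorrected: 1 − 0.42² × 0.68 − 0.58² × 0.32 = 1 − 0.120 − 0.108 = 77%.

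The article does not say which form is meant. Under either, a split is not rare, and for a pair with one arm on each side no test is named.

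**The case against.** The strongest reply is that the article never promises a 5% rate across all comparisons, never says that any significant pair wins, and points to an additional file with more protocol detail that is not shown. The deciding visit and contrast, and any adjustment, may be settled there. The Background also gives the arms distinct roles (sham comparator and waiting-list control), so a reader could take ta-VNS against tan-VNS as the main contrast. At one visit that single test has a 5% error rate. All of this stands, and it is why the figures are conditional.

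It also stands that the excess over three visits does not belong to Mann-Whitney alone. With Kruskal-Wallis first at each visit, 12.7% remains at ρ = 0.5, and nothing in the ANOVA route spans visits either.

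Three stronger readings are tempting, and the article does not support them:

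- That the trial's false-positive rate simply is some figure between 12% and 29%. This needs a success rule and a correlation that are not given, and 29% is not an upper limit.
- That the normality check produces the inflation. Step 3 shows otherwise.
- That the modified Engel scale is a second tested primary outcome. It may be only the way seizure outcomes are reported.

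The reply does not rescue the Mann-Whitney sentence. That is a rule the article states, and it does not fit three arms whatever the additional file contains.

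**Conclusion.** The point holds in limited form. The firm error is that a two-sample test is prescribed for a three-arm comparison, with no overall test or adjustment, beside a parametric route that has one. Its size is about 12% at one visit against a nominal 5%, given the stated arm sizes and if any significant pair counts. Extending the count to any of the three visits gives about 20% to 32% for ρ from 0.9 to 0. That range is an illustration under assumptions, not a property the article fixes.

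A second, separate fault is that the normality rule is worded by group, which leaves the method undefined when arms disagree. The absence of a named primary visit or contrast is not itself counted as an error, because the full protocol may supply it.

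**What to change.** Replace the Mann-Whitney sentence with: Kruskal-Wallis across the three arms, then pairwise Mann-Whitney tests only if it is significant. This brings the one-visit rate to about 5%. Choose the method once for all three arms together, rather than group by group, so that a split between arms cannot arise.

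Because Kruskal-Wallis alone still leaves about 13% over three visits at ρ = 0.5, also designate one of the listed visits as primary (for example month 6, the end of treatment) or adjust across visits, unless the full protocol already does so.

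The first two changes cost only wording. Designating a visit costs more: the other two visits lose the status of independent primary claims, and because the trial is registered and recruiting (35 of the planned 102 participants by 15 February 2015), the change should be recorded as a dated amendment before any unblinded look at the data. A particular regression model or a fixed testing order would be a matter of preference and is not needed to cure this error.

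### The only fallback named for non-normal data is an independent-samples test, so no rank test is fixed for the paired baseline-versus-after-treatment comparisons (minor)

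*Protocol article*

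**What the plan says.** The Primary outcomes section has each child contribute repeated values: "the baseline seizure frequency and the seizure frequency after 2 months, 4 months and 6 months of enrollment will be counted". Table 1 shows EEG, HRV and QOL at baseline and 6 months.

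The Statistical analysis section then gives these rules, in this order:

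- Before-after comparisons: "Comparison of seizure frequency, HRV and QOL between baseline and after treatment will be analyzed by paired-samples t-test". No condition is attached.
- Normality check: "The Kolmogorov-Smirnov test will be used to evaluate if groups fit normal distributions". Those that pass then go to parametric tests, in the plural.
- Between-arm comparisons: one-way ANOVA across the three arms, with Student–Newman–Keuls or Dunnett's T3 as the post-hoc test.
- The fallback, in the next sentence: "Non-normally distributed groups will be analyzed by Mann–Whitney’s test".
- Significance level, at the end of the section: "A *P* value <0.05 will be considered of statistical significance".

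Mann–Whitney is the only non-parametric test named. No paired rank test appears. The Randomization and blinding section gives 30 children in each stimulation arm and 42 in the control arm. The article states no effect size, standard deviation, within-child correlation or power.

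**The concern.** The section defines two kinds of comparison: within child over time, and between arms. It gives one fallback, which suits only independent samples. The text allows two readings.

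- **The fallback covers every comparison.** The normality check stands directly after the paired t-test sentence and leads to parametric tests in general. Skewed before-after data would then go to Mann–Whitney and the pairing would be lost. The check would also look at the wrong quantity, because a paired t-test depends on the distribution of within-child differences, not of the values at each visit.
- **The fallback covers only between-arm comparisons.** The paired t-test is then kept for skewed data, with no alternative named.

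At stake are the before-after statements for three outcomes. On the first reading, real changes could be reported as non-significant, by an amount that varies with each outcome's within-child correlation. On the second, the test remains valid but is weaker than it need be. HRV and QOL are the cleaner cases, because no entry criterion selects on them.

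**Working it through.** There is no power figure in the article to reproduce, so everything below rests on stated assumptions.

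**Inputs from the article.** n = 30 and n = 42 (Randomization and blinding); 0.05 (Statistical analysis; two-sided is assumed); a mean reduction of 54.13% in the pilot (Background); at least eight seizures in 2 months at entry (Inclusion criteria).

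**Assumed.** Within-child correlation ρ = 0.5, with 0.3 and 0.7 as alternatives; for counts, a median of 16 per 2 months, log-SD 1.0 and Poisson counting; reductions of 30% and 40% beside the pilot figure.

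**Step 1: normal approximation, n = 30, ρ = 0.5, shift of d SD.**

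- Paired test: power = Φ(d/√(2(1−ρ)/n) − 1.96). At d = 0.4: Φ(0.4/0.183 − 1.96) = Φ(0.23) = 59.1%.
- Unpaired test on the same pairs: power = Φ((d/√(2/n) − 1.96)/√(1−ρ)). At d = 0.4: Φ((1.549 − 1.96)/0.707) = Φ(−0.58) = 28.1%.
- Loss: 31 points at d = 0.4, 5 points at d = 0.8 (99.2% against 94.6%), and about 0 at d = 1.0.
- Real type I error of the unpaired test: 2Φ(−1.96/√0.5) = 2Φ(−2.77) = 0.56%.

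**Step 2: simulated lognormal pairs, n = 30, ρ = 0.5 on the log scale (4000 replicates).** Signed-rank against Mann–Whitney: 16.0% vs 4.4% at 0.2 SD, 49.0% vs 26.4% at 0.4 SD, 82.6% vs 64.6% at 0.6 SD and 97.3% vs 91.4% at 0.8 SD. The loss peaks at 23 points and is about 1 point at 1.0 SD. With n = 42 it peaks at 22. Mann–Whitney's real type I error is about 0.6% to 0.8%. The loss near 30 points therefore belongs to near-normal data, where the fallback would seldom be triggered; for skewed data the peak is nearer 23 at this correlation.

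**Step 3: simulated counts, n = 30, ρ = 0.5, no selection on baseline (6000 replicates).**

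| Reduction | Mann–Whitney | Signed-rank | Paired t |
|---|---|---|---|
| none | 0.8% | 5.1% | 4.1% |
| 30% | 18.0% | 35.8% | 27.1% |
| 40% | 42.5% | 62.6% | 49.0% |
| 54.13% | 83.9% | 92.8% | 82.0% |

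Mann–Whitney loses 17.8, 20.1 and 8.9 points against signed-rank. The paired t-test loses 8.7, 13.6 and 10.8. For a 40% reduction, Mann–Whitney against signed-rank is 41.6% vs 49.7% at ρ = 0.3 and 40.4% vs 79.6% at ρ = 0.7.

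**Step 4: the same counts with the entry floor.** About 24% of the children simulated in step 3 have a baseline below eight and could not enrol. Keep only those with at least eight, taking the qualifying count as the analysed baseline and setting ρ before selection. At ρ = 0.5, Mann–Whitney against signed-rank becomes 70.9% vs 70.4%, 89.9% vs 88.0% and 99.6% vs 99.2% for the three reductions: the loss is gone. With no true effect, Mann–Whitney rejects in about 8% to 9% of trials and signed-rank in about 10% to 12%, because children selected for a high count tend to fall back towards their usual level. At ρ = 0.7 a loss of about 17, 7 and 0 points remains, against 37, 38 and 11 without the floor.

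**The case against.** **The between-arm reading is at least as natural.** The fallback sentence follows the three-arm ANOVA, and elsewhere in the article a group is a randomized arm, never a visit. On that reading, checking normality by arm is not misdirected either. This stands, and it is why the point is put as two readings. The text does not establish that Mann–Whitney will be run on before-after data.

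**Silence about a paired rank test may be filled elsewhere.** The article refers to an additional file with more detail, and a SAP may exist. This stands in part: a missing fallback alone would not be a finding. But the article does fix a detailed scheme, with a normality test, a paired test, post-hoc tests and one fallback, and read literally that scheme puts paired data into an independent-samples test.

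**The retained paired t-test is not invalid.** Its null rejection in step 3 is 4.1%. That also stands; on the second reading the cost is power alone.

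**The tempting stronger reading.** A reader might infer from step 3 that the plan loses 9 to 20 points of power on the primary outcome and that its error rate there is far below 0.05. The documents do not support this. The range reflects three chosen effects in one assumed model, and step 4 shows that the article's own entry criterion can remove the loss and push null rejection above 5%. The Primary outcomes section also expresses seizure outcomes on a modified Engel scale, which the count model does not represent.

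**Conclusion.** The point holds as a minor one. The plan names no rank test suited to paired data, and its single fallback is wrong for such data if applied to them.

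- **If Mann–Whitney is used on before-after data:** at an assumed correlation of 0.5, n = 30 and no selection on baseline, type I error is about 1% instead of 5%, with roughly 0 to 30 points of power lost depending on effect and distribution.
- **If the paired t-test is kept:** it has about 27%, 49% and 82% power against 36%, 63% and 93% for signed-rank in the step 3 model.

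These figures illustrate outcomes without selection on baseline, such as HRV and QOL, to the extent that those are skewed and correlated as assumed. They do not carry over to seizure frequency, where regression to the mean from the entry floor can inflate null rejection in any before-after test, signed-rank included.

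The consequence is limited because these are uncontrolled within-arm comparisons. The trial's question, ta-VNS against sham and waiting list, is answered between arms.

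**What to change.** In the Statistical analysis section:

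1. Limit Mann–Whitney to comparisons between independent groups.
2. For baseline-versus-after-treatment comparisons of seizure frequency, HRV and QOL, name the Wilcoxon signed-rank test on within-child differences when these are not normal.
3. Make any normality check for those comparisons on the within-child differences.
4. Label the within-arm comparisons descriptive and secondary to the between-arm comparison. This matters most for seizure frequency, because changing the test does not cure regression to the mean.

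The cost is a few sentences. The signed-rank test is available in the software already named, and no new data, patients or procedures are needed.

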## Discussion

Vagus nerve stimulation (VNS) is effective in refractory epilepsy and depression, and is being investigated in heart failure, headache, gastric motility disorders and asthma [4]. In addition to the suppression of seizure frequency, QOL of the pediatric patients with epilepsy also improved by VNS [14]. In patients with drug-resistant focal epilepsy, VNS reduces cardiac electrical instability, potentially by improving autonomic imbalance in favor of parasympathetic dominance [15]. Nonetheless, adverse events are generally associated with implantation or continuous on-off stimulation, including infection, bradycardia, vocal cord paresis, voice alteration, cough, headache, dyspnea, pharyngitis and pain [4].

As the only peripheral branch of the vagus nerve, the ABVN has been suggested as a target of transcutaneous vagus nerve stimulation (t-VNS). In comparison with VNS, t-VNS is more economic with less side-effects. Particularly for pediatric patients, transcutaneous stimulation is preferred. In addition to epilepsy, ta-VNS is now being investigated in anti-atrial fibrillation [16], depression [17] and tinnitus [18]. It has been reported that in healthy participants, active t-VNS significantly increased HRV and reduced sympathetic nerve outflow [19]. Yet the relationship between the anticonvulsive effect of ta-VNS and the improvement of autonomic imbalance needs to be further investigated.

Although the mechanism of the anticonvulsive effect of VNS is unclear, it has been suggested to be mediated via vagal afferent projections to the nucleus tractus solitarius (NTS), then via pathways from the NTS to other brain structures which correlate with the pathogenesis of epilepsy [20]. Animal studies have shown an anatomical relationship between the ABVN and the NTS, and ta-VNS significantly suppressed epileptiform activity in EEG traces via increasing the firing rates of the neurons of the NTS [21]. Studies in humans have shown that auricular conchae stimulation produced significant activation of the central vagal projections including widespread activity in the ipsilateral NTS [22]. The NTS receives and integrates visceral autonomic afferent information, which indicates the possibility of the NTS participating in the anticonvulsive effect of ta-VNS.

Currently, there are no RCTs investigating ta-VNS for pediatric patients with epilepsy. Here, we designed this study to conduct a RCT to examine the potential effect of ta-VNS and its possible mechanism.

## Trial status

This trial is currently recruiting participants. To date (15 February 2015), 35 participants have been recruited.

## Abbreviations

ABVN: Auricular branch of the vagus nerve
ANOVA: Analysis of variance
CBCL: Child Behavior Checklist
CONSORT: Consolidated Standards of Reporting Trials
EEG: Electroencephalogram
FDA: US Food and Drug Administration
HRV: Heart rate variability
NTS: Nucleus tractus solitarius
QOL: Quality of life
RCT: Randomized controlled trial
RMSSD: Root mean square of successive differences
SDNN: Standard deviation of normal-to-normal interval
tan-VNS: Transcutaneous auricular non-vagus nerve stimulation
ta-VNS: Transcutaneous auricular vagus nerve stimulation
t-VNS: Transcutaneous vagus nerve stimulation
VNS: Vagus nerve stimulation
